### Data management

All data will be collected via Virtual Clinic software and stored on a secure Virtual Clinic server. All information collected by the software is coded with either a participant identification number or an email address to facilitate data-to-patient matching. Clinical information not obtained from the online application, including diagnostic status using the MINI, is collected by interview via telephone and stored in written format in a secure location at CRUfAD. Any identifiable information collected remains confidential, except as required by law. Only members of the site (CRUfAD) research team will have access to participant information and data in order to monitor patient progress. During data analysis, re-identifiable data (i.e. coded data) will be used. At study completion, non-identifiable data will be written to a password-protected database. All data will be extracted from the Virtual Clinic servers in the form of an Excel-compatible file to be transferred to the IBM Statistical Package for the Social Sciences (IBM SPSS, IBM Corp., Armonk, NY, USA) by a member of the research team.

Participants will be informed in writing that the research team plans to disseminate the trial results in peer-reviewed scientific publications and presentations. Participants are informed that in any such dissemination, their anonymity will be maintained.

Participants will be sent (via email) a written summary of the results in lay terms following completion of the trial study phase.

### Statistical methods

Power calculations were informed by calculation of effect size data from Spence et al. [20], providing a between-group effect corresponding to Hedges’ g of 0.47. The minimum sample size for each group (alpha set at 0.05, power at 0.80) was identified as 72, but at least 10 % more will be recruited to hedge against expected attrition. All analyses will be conducted at conclusion of the trial period (i.e. after all participants in the treatment group have completed the iCBT program). Significance testing of group differences regarding demographic data and pre-treatment measurements will be conducted using analysis of variance (ANOVA) and χ2 where the variables consist of nominal (or categorical) data. Intent-to-treat (ITT) mixed models using restricted maximum likelihood (REML) estimation will be used to account for missing data due to participant drop-out. Mixed models do not assume that the last measurement is stable (the last observation carried forward assumption) [63]. REML models are appropriate for RCTs with multiple time points and pre-to post-only designs [64]. The assumption that data are missing at random (MAR) will be evaluated using binary logistic regression to predict drop-out (0 = no drop-out, 1 = drop-out) and by comparing these two groups on baseline measures. Significant effects will be followed up with pairwise contrasts comparing mean pre-treatment to mean post-treatment scores. Complete-case analyses of the primary hypotheses using data from participants who complete all six lessons of the PTSD program will also be conducted. The effect of potential treatment moderators (e.g. time post-trauma, number of traumatic events) will be evaluated by including baseline variables of interest as a covariate and interaction term in separate mixed models analyses. Analyses will be performed in IBM SPSS version 21. Effect sizes will be calculated between groups (Hedges’ g) and within groups (Cohen’s d, adjusting for the repeated measures correlation) using the pooled standard deviation and adjusted for sample size.

Mediation analyses will be used to examine the association between change in PTSD symptoms over treatment and change in each of IU and emotion regulation in separate analyses. Tests of the indirect effects (mediation) will be conducted using PROCESS [65]. This method was chosen over the causal steps approach [66] based on recent research advocating the use of modern statistical approaches to quantify intervening variable models [67]. As recommended, particularly for small samples, estimates of indirect effects will be generated using bootstrapping analysis see [68, 69]. Bootstrapping is a nonparametric resampling method that generates an estimate of the indirect effect, and does not require assumptions about the shape of the sampling distribution that underlie the Sobel test. In bootstrapping analysis, the most stringent test of an indirect effect (mediation) is if the 95 % bias corrected and accelerated confidence intervals for the indirect effect do not include the value of 0. When zero is outside of the 95 % confidence interval estimate, the indirect effect is declared statistically different from zero at *p* < 0.05 (two-tailed), indicating that the effect of the independent variable on the dependent variable is contingent upon the effect of the proposed mediator [68]. In the current study, PROCESS for SPSS will be used to estimate 5000 bias-corrected bootstrap 95 % confidence intervals.

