**Methods/Design:**

Patients with PTSD will be recruited via the research arm of a not-for-profit clinical and research unit in Australia and randomised to a treatment group or waitlist control group. The minimum sample size for each group (alpha 0.05, power 0.80 for a *g* of 0.47) was identified as 72, but 10 % more will be recruited to hedge against expected attrition. PTSD diagnosis will be determined using the PTSD module from the Mini International Neuropsychiatric Interview version 5.0.0. The PTSD Checklist – Civilian version (PCL-C) will be used to measure PTSD symptoms (the primary outcome measure), with the Intolerance of Uncertainty Scale 12-item version (IUS-12) and the Emotion Regulation Questionnaire (ERQ) used to measure intolerance of uncertainty and emotion regulation, respectively. The PCL-C will be administered to the treatment group before each lesson of the PTSD program and at 3-month follow-up. The IUS-12 and ERQ will be administered before lessons 1 and 4, at post-treatment and at 3-month follow-up. The waitlist control group will complete these measures at week 1, week 5 and week 11 of the waitlist period. PTSD program efficacy will be determined using intent-to-treat mixed models. Maintenance of gains will be assessed at 3-month follow-up. Mediation analyses using PROCESS will be used to examine the association between change in PTSD symptoms over treatment and change in each of IU and emotion regulation ability in separate analyses.

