### Objectives

The current Standard Protocol Items: Recommendations for Interventional Trials (SPIRIT)-compliant [34] protocol outlines the methodology of a CONSORT-compliant [35] RCT, the primary objective of which is to establish the efficacy of the iCBT program for PTSD. Secondary objectives are to examine change in IU and emotion regulation ability following the iCBT program and the association between change in each of these constructs and PTSD symptom change following the PTSD program.

The proposed iCBT program aims to reduce psychological distress and PTSD symptoms in those with PTSD. It comprises psychoeducation about the trauma reaction and how it is maintained after the event by particular patterns of thinking, feeling and behaving. Dearousal skills are taught and practiced. Participants are taught ways to identify and change unhelpful thoughts about the trauma. They will be habituated to their challenging trauma memories using a series of brief structured writing assignments and taught graded exposure methods to re-enter feared situations. Finally, relapse prevention will cover continued skills practice and instruction on independent management of potential future setbacks. These elements have been incorporated into standard CBT-based treatment for PTSD both in internet and face-to-face formats [12, 18–21, 36–38], but have been adapted for the proposed internet treatment program.

Hypotheses are as follows: (1) patients receiving iCBT for PTSD will show greater mean symptom reduction on a standardised PTSD measure than a waitlist control group during treatment and at the end of treatment (the primary endpoint), with preserved symptom reduction at 3-month follow-up; (2) IU will be less at post-treatment than pre-treatment; (3) reduction in IU over treatment will be associated with reduction in PTSD severity; (4) emotion regulation will be greater at post-treatment than pre-treatment; and (5) increased emotion regulation after treatment will be associated with reduced PTSD severity after treatment.

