### Primary outcome measures

Administration time points for all instruments are contained in Table 1.

**Table 1 Tab1:** Administration time points for questionnaires used in the RCT

	Administration time point				
Measure	Pre-treatment	Before each lesson	Mid -treatment^d^	Post-treatment^e^	3-month follow-up^f^
LEC^a^	♦				
DES	♦				
MINI	♦				♦
PCL-C^b^	♦	♦	♦	♦	♦
BDI-II^c^	♦		♦	♦	♦
PHQ-9	♦		♦	♦	♦
K10	♦	♦	♦	♦	♦
GAD-7	♦		♦	♦	♦
CEQ	♦			♦	
IUS-12	♦		♦	♦	♦
ERQ	♦		♦	♦	♦
SUDOR	♦		♦	♦	♦
SAPAS	♦				

*LEC* Life Events Checklist, *DES* Dissociative Experiences Scale, *MINI* Mini International Psychiatric Interview, *PCL-C* PTSD Checklist **–** Civilian version, *BDI-II* Beck Depression Inventory – Second Edition, *PHQ-9* Patient Health Questionnaire 9-item version, *K10* Kessler Psychological Distress Scale 10-item version, *GAD-7* Generalised Anxiety Disorder 7-Item Scale, *CEQ* - Credibility and Expectancy/Satisfaction Questionnaire, *IUS-12* Intolerance of Uncertainty Scale 12-item version, *ERQ* Emotion Regulation Questionnaire, *SUDOR* Service Utilisation and Days Out of Role Questionnaire, *SAPAS* Standardised Assessment of Personality - Abbreviated Scale

^a^Refers to both LEC-IV and part 2 of LEC-5

^b^Includes items 10, 11, and 16 from PCL-5

^c^Item 9 only

^d^Waitlist control group completes these measures at week 5 of the waitlist period

^e^Waitlist control group completes these measures at week 11 of the waitlist period

^f^Treatment group only

**Posttraumatic stress disorder Checklist – Civilian version** (PCL-C) [40]. The PCL-C is a 17-item self-report questionnaire providing a continuous measure of PTSD symptomatology, conforming to Diagnostic and Statistical Manual of Mental Disorders, Fourth Edition (DSM-IV) diagnostic criteria. Each item reflects a PTSD symptom and is rated on a 5-point scale for distress (1 = “Not at all”; 5 = “Extremely”). Items 10, 11 and 16 from the PCL-5 [41] will also be administered, which assess new diagnostic criteria for PTSD in the fifth edition of the DSM [DSM-5 1]. This approach was adopted in favour of sole use of the PCL-5, which had not been validated at the time of trial design. This will enable examination of change in the new PTSD symptoms in DSM-5.

**PTSD diagnostic status**. Change in PTSD diagnostic status will be indexed using the MINI PTSD module. The MINI has sound reliability and validity psychometrics [39].

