### Participant monitoring

The Clinical Trials Manager of CRUfAD and a member of the research team will oversee participant monitoring. Symptom severity of the target disorder and general distress levels are measured before, during, and immediately upon completing the PTSD program based on empirically validated standardised internet-delivered symptom measures. Participants will be sent automated emails at the completion of each lesson to encourage skills practice. Patient queries throughout the program are primarily addressed by email contact from the clinician (AA) or the Clinical Trials Manager (JS). If clinically indicated, or if a patient’s K10 and/or PHQ9 or PCL-C scores deteriorate, the clinician makes telephone contact. If a participant misses a lesson, a member of the research team will send an email reminder (via the Virtual Clinic system) or will make telephone contact to remind the participant to complete the lesson.

The treatment group will be required to complete the iCBT program within 10 weeks to remain in the trial. Adherence is monitored throughout the program. Once enrolled, a participant can elect to discontinue at any time. A participant may be withdrawn from the trial (typically meaning course access will be closed) for the following reasons: lack of computer and internet access; change in prescribed medication for anxiety or depression; change in medication status of exclusion medications; suicidality or clinical risk; failure to complete baseline questionnaires; failure to commence the PTSD program. Lack of adherence throughout the iCBT program is not a specified reason for participant withdrawal, although a participant may withdraw voluntarily. Those in the waitlist control group will be required to complete questionnaires at weeks 1, 5 and 11 of the waitlist period to remain in the RCT. The waitlist control group will have access to the iCBT program immediately at the conclusion of the waitlist period. All reasons for withdrawal status will be documented.

To promote participant retention, participants are reminded that data collection is an important aspect of research and enables the research team to track their progress and to evaluate the program. Any adverse events will be reported to the Director of CRUfAD (GA) and to the Human Research Ethics Committee (HREC) of St Vincent’s Hospital, the responsible body for initiating a clinical trial audit.

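### The stated trigger for all analyses, completion of iCBT by the treatment group, falls about three months before the planned follow-up PCL-C and the only post-baseline MINI

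*Protocol article*

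**What the plan says.** The timing rule is one sentence in Statistical methods: "All analyses will be conducted at conclusion of the trial period (i.e. after all participants in the treatment group have completed the iCBT program". It covers every analysis, and it defines the end of the trial period by program completion in one arm.

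Other parts of the article set what has to be analysed, and when:

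- **Objectives, hypothesis 1.** The between-group contrast applies "during treatment and at the end of treatment (the primary endpoint"), and the same hypothesis continues "with preserved symptom reduction at 3-month follow-up".
- **Abstract, Methods/Design.** "Maintenance of gains will be assessed at 3-month follow-up". On the schedule: "The PCL-C will be administered to the treatment group before each lesson of the PTSD program and at 3-month follow-up".
- **Primary outcome measures and Table 1.** Change in PTSD diagnostic status, measured with the MINI, is listed as a primary outcome. Table 1 marks the MINI at pre-treatment and at 3-month follow-up only, and its footnote f limits that follow-up to the treatment group. For the post-treatment column, footnote e says: "Waitlist control group completes these measures at week 11 of the waitlist period".
- **Participant monitoring.** "The treatment group will be required to complete the iCBT program within 10 weeks to remain in the trial".
- **Trial status.** Data collection is expected to finish in September 2016. This date is not linked to the analysis trigger.

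No other section sets a separate or later date for the follow-up analyses.

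**The concern.** The rule and the schedule cannot both be followed to the letter. At the moment when the last treated participant finishes the program, everyone in that arm who finished within the preceding three months still has the 3-month PCL-C and MINI ahead of them. An analysis at that moment would leave them out of the maintenance analysis. They would also have no post-baseline value at all on diagnostic status.

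The plan justifies its mixed models as a way to handle data missing through drop-out. These gaps would come from the analysis date, and they would fall on the most recently enrolled. If the team instead waits for follow-up, which is the sensible course, it departs from the only timing rule the article states.

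The rule also says nothing about the waitlist arm, whose post-treatment forms are half of the primary between-group comparison.

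**Working it through.** **Plan's own figure, used only to size the arm.** Statistical methods gives g = 0.47, alpha 0.05 and power 0.80. With a two-sided test, n per group = 2 × (1.960 + 0.842)² / 0.47² = 15.70 / 0.2209 = 71.1, rounded up to 72. This reproduces the stated 72. With 10% more, 72 × 1.10 = 79.2, so 80 per group. Nothing in the timing conflict depends on this number.

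**Timeline for the last treated participant.** Let week 0 be that participant's start.

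- Program end, and so the trigger: week 10 at the latest (Participant monitoring).
- 3-month follow-up: the article does not say what it is counted from. I assume program end and 12 to 13 weeks, which gives week 22 to 23.
- Gap between trigger and last follow-up data: 12 to 13 weeks.

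**Timeline for the waitlist arm.** Measures are taken at weeks 1, 5 and 11, with week 1 as baseline. From week 1 to week 11 is 11 − 1 = 10 elapsed weeks, the same as the program. A waitlist participant who starts alongside the last treated participant is therefore due at about the trigger. One who starts L weeks later is due about L weeks after it. One who starts earlier is due before it.

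**How many treated participants fall inside the gap.** This needs an accrual pattern, which the article does not give. The figures below assume that enrolment starts on 13 September 2014, that follow-up ends on 30 September 2016, that everyone takes 10 weeks over the program, and that the treatment arm has 80 participants.

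- Calendar span: 748 days / 7 = 106.9 weeks.
- Accrual window: 106.9 − 10 − 13 = 83.9 weeks (84.9 weeks if follow-up is at 12 weeks).

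*Even accrual.* 80 / 83.9 = 0.954 per week; × 13 = 12.4, or 15.5% of 80. With 12 weeks: 80 / 84.9 × 12 = 11.3, or 14.1%.

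*Slow early accrual.* Trial status reports 26 eligible participants to date and a submission date of 19 June 2015, which is 279 / 7 = 39.9 weeks after the first enrolment. Assume that the count refers to that date and that all 26 were randomised.

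- Remaining window: 83.9 − 39.9 = 44.0 weeks.
- Required rate: (160 − 26) / 44.0 = 3.05 per week over both arms, or 1.52 in the treatment arm.
- Inside the gap: 1.52 × 13 = 19.8, or about 25% of 80.
- With 12 weeks: (134 / 45.0) / 2 × 12 = 17.9, or about 22%.

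**The case against.** The strongest reply is that the sentence sets only an earliest time. Its natural purpose is to rule out analyses during the trial. An article that schedules 3-month measures, plans to assess maintenance and gives an end date for data collection plainly means to use those data. Exact data cuts are usually left to the analysis plan. Part of this stands: nothing in the article says that follow-up data will be discarded, and a reader who infers such an intention goes too far. But the article does not leave timing open. It states a rule for every analysis and spells out that the trial period ends at program completion. The September 2016 date is not tied to analysis. A stated rule that conflicts with the schedule is different from a detail left out.

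Three stronger readings are tempting, and the documents do not support them.

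- **That the waitlist arm's primary endpoint generally falls after the trigger.** Week 11 sounds later than a 10-week program, but baseline is week 1, so the elapsed time is the same. Only a waitlist participant who starts later than the last treated participant could be missed, and the article does not give the order of enrolment.
- **That the trigger can never be met, because non-adherent participants stay in.** Participant monitoring does say "Lack of adherence throughout the iCBT program is not a specified reason for participant withdrawal", but the same paragraph also requires completion within 10 weeks to remain in the trial, which bounds the period. Those two sentences need to be reconciled, but that is a separate matter from analysis timing.
- **That early analysis would unblind or bias the follow-up.** The 3-month follow-up is in the treatment group only, so no randomised comparison rests on it. Participants are not blinded in any case, the PCL-C is self-reported, and the follow-up interviewers are independent of the study. The article describes no early look followed by a choice of analysis date.

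**Conclusion.** The point holds as a conflict between the stated analysis trigger and the article's own assessment schedule. It is certain for the treated participants who finish last: their 3-month PCL-C and their only post-baseline MINI come about 12 to 13 weeks after the trigger, if follow-up is counted from program end. It affects the maintenance part of hypothesis 1 and an outcome listed as primary.

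The number affected is not known. Even accrual gives about 11 to 12 of 80 (14 to 16%), but the 26 eligible participants in Trial status do not suggest even accrual. A slow start gives about 18 to 20 of 80 (22 to 25%). Both are illustrations, and the conflict does not depend on either.

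The primary end-of-treatment comparison is not materially threatened. The treatment arm's data are in at about the trigger, and the waitlist arm's are too unless someone in that arm starts later than the last treated participant. This is a wording defect that should be corrected, not a flaw in the design.

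**What to change.** Replace the timing sentence with two data cuts:

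1. The pre-, mid- and post-treatment analyses, including the primary PCL-C comparison, run once the last randomised participant in either arm has passed the post-treatment or week-11 window, whether or not the program was completed.
2. The maintenance and MINI analyses run once the last treatment-group participant has passed the 3-month window.

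Alternatively, state that all analyses run at the second point.

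The change takes one or two sentences. It alters no sample size, assessment or treatment rule. The cost is a wait of about three months for the follow-up analyses, or for all of them under the alternative.

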### Trial design and blinding

The trial is a randomised controlled superiority trial with two parallel arms using a 1:1 allocation ratio. Participants will not be blind to their group allocation. Follow-up interviews will be conducted by clinicians independent of the study and therefore blind to group allocation.

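### The protocol plans significance tests of baseline differences and names no baseline adjustment for the primary PCL-C comparison; adjusting would cost almost nothing and, depending on the pre-post correlation, could add useful power

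*Protocol article*

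**What the plan says.** All of this is in the protocol article; no analysis plan is at hand.

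- **Baseline tests.** Statistical methods: "Significance testing of group differences regarding demographic data and pre-treatment measurements will be conducted using analysis of variance (ANOVA"), with chi-square for nominal or categorical variables.
- **Main model.** The same section specifies intent-to-treat mixed models fitted by REML. It does not list the fixed effects, the covariance structure or any constraint on the baseline means. The follow-up step is: "Significant effects will be followed up with pairwise contrasts comparing mean pre-treatment to mean post-treatment scores".
- **Baseline covariates.** They are mentioned once, for potential treatment moderators, which are to be examined "by including baseline variables of interest as a covariate and interaction term in separate mixed models analyses".
- **Sample size.** It rests on a Hedges' g of 0.47 between groups, taken from earlier trial data: "The minimum sample size for each group (alpha set at 0.05, power at 0.80) was identified as 72". A further 10% or more is added for attrition. Trial design and blinding gives "two parallel arms using a 1:1 allocation ratio".
- **Data available.** Table 1 has PCL-C at pre-treatment, mid-treatment and post-treatment. For the waitlist arm the Abstract says: "The waitlist control group will complete these measures at week 1, week 5 and week 11 of the waitlist period". A pre-treatment PCL-C therefore exists in both arms.
- **Primary endpoint.** Under Objectives, hypothesis 1 concerns greater mean PTSD symptom reduction than waitlist, with the end of treatment as the primary endpoint.

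**The concern.** Two things are at issue, one stated and one inferred.

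**Stated: the baseline significance tests.** Allocation is randomised and concealed in sealed opaque envelopes, so any difference between arms at baseline is due to chance. A significance test then addresses a null hypothesis known to be true. A non-significant result does not show that an imbalance in a prognostic score is harmless.

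**Inferred: the role of pre-treatment PCL-C in the primary model.** A pre-treatment mean can be contrasted with a post-treatment mean inside the model only if pre-treatment is a level of time. The remark that REML models suit designs with only a pre and a post measurement, and the wording of hypothesis 1 as symptom reduction, point the same way. No baseline adjustment is named for the main comparison. If the arm means are free at baseline, the group-by-time effect at post-treatment is a difference between arms in mean change.

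What is at stake is the precision of the primary estimate, and likewise that of PHQ-9, K10, GAD-7, IUS-12 and ERQ, which also have pre-treatment values in both arms.

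**Working it through.** **Inputs from the protocol:** g = 0.47 between groups; alpha 0.05 and power 0.80; 72 per arm; 1:1 allocation. **Assumed, because the protocol does not give them:** the pre-post correlation rho, equal pre and post SDs (relaxed in step 4), and g expressed in post-treatment SD units.

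**Step 1. Reproduce the stated sample size.** By the normal approximation, n per arm = 2(1.960 + 0.842)² / 0.47² = 71.1, rounded up to 72. This matches. A one-sided test would need only 56, so the figure is two-sided. With the noncentral t distribution, power at 72 per arm is 0.7998, or 80.0%. The stated 72 is therefore the size for an unadjusted comparison of post-treatment scores.

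**Step 2. Variance of each form of the comparison, relative to the post score alone (= 1).**

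- Difference in change (baseline means free): 2(1 − rho)
- Baseline-adjusted (covariate, or common baseline mean): 1 − rho²
- Excess of the first over the second: 2(1 − rho) − (1 − rho²) = (1 − rho)², which is never negative

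A generalised least squares calculation with three common time points and compound symmetry gave the same factors: 1.40 and 0.91 at rho 0.3, 1.00 and 0.75 at 0.5, 0.60 and 0.51 at 0.7.

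**Step 3. Power at 72 per arm.** The noncentrality parameter is 0.47 × sqrt(72/2) / sqrt(factor) = 2.82 / sqrt(factor).

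| rho | change: factor, noncentrality, power | adjusted: factor, noncentrality, power | gain (points) |
|---|---|---|---|
| 0.3 | 1.40, 2.38, 65.8% | 0.91, 2.96, 83.6% | about 18 |
| 0.5 | 1.00, 2.82, 80.0% | 0.75, 3.26, 89.9% | 9.9 |
| 0.6 | 0.80, 3.15, 87.9% | 0.64, 3.53, 93.8% | 5.9 |
| 0.7 | 0.60, 3.64, 95.1% | 0.51, 3.95, 97.5% | 2.4 |

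At rho 0.5 the change form has the variance of the post-only comparison, so it just meets the planned power. Below 0.5 it falls short. At rho 0.5 the adjusted form would need 54 per arm for 80% power instead of 72 (normal approximation).

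**Step 4. Unequal SDs.** Let k = pre SD / post SD. The change factor becomes 1 + k² − 2 × rho × k, and the excess over adjustment becomes (k − rho)². With a post SD 1.25 times the pre SD, k = 0.8. At rho 0.5 the factor is 1 + 0.64 − 0.80 = 0.84. Power is then 86.3% against 89.9%, a gain of 3.6 points. With this ratio the change form falls below 80% only for rho under 0.4, where 1 + 0.64 − 0.64 = 1.

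**Step 5. Recruited number.** 72 × 1.10 = 79.2, or 80 per arm. With no attrition and rho 0.5, power is 84.0% for change and 92.7% adjusted.

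**Step 6. Chance imbalance.** The standard error of the baseline difference is sqrt(2/72) = 0.167 SD. Given an imbalance b, the change contrast is shifted by −(1 − rho)b. For b of one standard error and rho 0.5, that is 0.5 × 0.167 = 0.083 SD. Over repeated randomisations these shifts average to zero. Their variance is (1 − rho)² × 2/72, which is exactly the excess in step 2. It is the same loss seen from another side, not an additional bias.

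**The case against.** The strongest objection is that the model is not specified. The article lists no fixed effects, and a condensed article may leave them to a fuller plan. The pre-to-post contrasts are equally available from a model with a common baseline mean, and under that model the loss is zero. The sentence on separate models is about moderators, with time since trauma and number of events as examples; it does not exclude pre-treatment PCL-C from the main model. All of this stands. It means that the form of the primary model must be put as a natural reading and the power loss as conditional on it.

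A second objection also stands. The size depends on a correlation that the protocol does not give, and at rho 0.5 the less efficient form still delivers the planned 80%.

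Three stronger readings are tempting but not supported:

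- **That the baseline tests replace adjustment, or decide which covariates enter.** No stated rule links the tests to the primary model. They do not alter its estimate or its error rate.
- **That the primary estimate is biased.** Under randomisation a difference in change scores is unbiased (step 6).
- **That the trial gives up some 10 points of power as a matter of fact.** That figure belongs to rho 0.5 with equal SDs. The gain runs from about 18 points at rho 0.3 to 2.4 at rho 0.7.

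The objection does not remove two facts: the protocol commits itself to uninformative baseline tests, and it names no adjustment for a prognostic score already collected in both arms.

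**Conclusion.** The point holds as a low-cost improvement in efficiency and a clarification of the primary model; it does not show an invalid analysis or an underpowered trial. The planned baseline significance tests are stated outright and serve no purpose in a randomised comparison. Pre-treatment PCL-C as an unadjusted level of time is the natural reading of the text, not a stated specification.

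The size is conditional on arm means being free at baseline. With equal SDs, adjustment is worth at least 5 points of power for rho up to about 0.6 and little above that. The calculations take 72 analysed per arm and g = 0.47 as planned. Adjustment cannot do worse in large samples; here its only statistical price is a trivial loss of degrees of freedom.

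**What to change.** In Statistical methods:

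1. State that the primary mixed model adjusts for pre-treatment PCL-C. One form takes mid- and post-treatment PCL-C as outcomes, with arm, time, arm-by-time, baseline PCL-C and baseline-by-time as fixed effects. The other keeps pre-treatment as an outcome level and constrains the arm means to be equal there.
2. State that the arm difference at post-treatment from that model is the primary estimate.
3. Use the same form for the secondary scales measured at pre-treatment in both arms, each with its own baseline value.
4. Replace the ANOVA and chi-square comparisons of arms at baseline with a descriptive table.

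If a fuller plan already specifies a common baseline mean or a baseline covariate, saying so settles items 1 to 3 wherever it applies.

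**Cost.** A few sentences, written before outcome data are analysed. No new data, participants or software are needed, since SPSS mixed models can fit either form. The price is one or two extra fixed effects, negligible with about 144 participants (2 × 72). The covariate form also needs a non-missing baseline value, which the equal-means form does not.
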